## Abstract

**Background:**

Malaria infection during pregnancy (MIP) is not only deleterious to the woman, but it also puts her fetus at increased risk of adverse outcomes, such as preterm delivery, low birth weight, and intrauterine growth retardation. Additionally, all-cause mortality during the first year of life in babies born to women with malaria during pregnancy is also increased. Many interventions such as IPTp-SP and long-lasting insecticidal nets have proven to be efficient at reducing malaria in pregnancy burden but adherence to recommended policies remains poor. In sub-Saharan Africa, malaria in pregnancy is often asymptomatic and many malaria infections may be missed due to the inadequate performance of the current rapid diagnostic test to detect low-level parasitemias. Therefore, additional strategies such as intermittent screening with ultrasensitive rapid diagnostic tests and treatment with an effective artemisinin-based combination therapy in addition to IPTp-SP could reduce placental malaria, peripheral malaria infection at delivery, and low birth weight.

**Methods:**

This pilot 2-group randomized open trial with a nested qualitative social behavioral will be carried out in Nanoro district in which 340 pregnant women will be recruited. Pregnant women will be randomized into two groups and followed on a monthly basis until delivery. In the intervention group, monthly screening using ultrasensitive rapid diagnostic tests and treatment of those found to be infected with dihydroartemisinin-piperaquine will be performed. In addition, a reminder will be sent to increase the uptake of IPTp-SP doses per woman. During scheduled and unscheduled visits, malaria infection, hemoglobin level, and other clinical outcomes will be assessed and compared by the group. The primary feasibility outcome will evaluate the study site's capacity to enroll participants and the women’s perception and acceptability of the intervention. The primary clinical outcome will be the prevalence of placental malaria at delivery.

**Discussion:**

The present protocol aims to evaluate the feasibility on a large-scale and also to demonstrate the impact and the operational feasibility of additional screening with ultrasensitive rapid diagnostic tests and treatment with DHA-PQ on placental malaria, low birth weight, and peripheral malaria infection at delivery in a high-burden setting in Burkina Faso.

**Trial registration:**

ClinicalTrials.gov, ID: NCT04147546 (14 October 2019).

## Introduction

Malaria remains a major preventable cause of morbidity, mortality, and adverse birth outcomes in sub-Saharan Africa (sSA). By using a model, Walker and colleagues estimated that without pregnancy-specific interventions in sub-Saharan Africa, 9.5 million pregnant women would have been exposed to infection, leading to 750,000 low birth weight (LBW) deliveries [1]. In areas of stable transmission, parasitemic pregnant women are rarely symptomatic and that severe disease or death from malaria is extremely unusual due to the acquisition of significant levels of anti-malarial immunity [2]. In these regions, the risk of *Plasmodium falciparum* infection increases when women get pregnant, with potential adverse consequences for mothers and their offsprings. Placental sequestration is more common in *P. falciparum* infections [3, 4]. Primigravidae women have the highest risk for malaria infection [5, 6], and malaria infections are associated with maternal anemia and adverse birth outcomes, including fetal loss, intrauterine growth retardation, and preterm delivery [7–11]. Malaria prevalence is highest in the first and second trimester of pregnancy [7] and the risk might not immediately return to pre-pregnancy levels after delivery [12]. To prevent the adverse effects of malaria in pregnancy (MiP), the World Health Organization (WHO) recommends a strategy based on three pillars: insecticide-treated nets (ITNs), effective case management of malarial illness and anemia, and intermittent preventive treatment in pregnancy with sulfadoxine–pyrimethamine (IPTp-SP) [13]. The latter involves the administration of curative doses of antimalarials at predefined intervals (ideally on a monthly basis, with a minimum number of 3 doses) irrespective of malaria infection [14, 15] during the second and third trimesters in malaria-endemic regions. IPTp has been proven to have a great impact on placental malaria (PM), LBW, peripheral malaria infection at delivery, and infant mortality so increasing the number of IPTp-SP doses given is a priority. In Burkina Faso, the National Malaria Control Program (NMCP) has recommended at least 3 doses of IPTp-SP but available information suggests that only 31.5% of eligible women met this recommendation despite observed high levels of antenatal clinic (ANC) attendance [1, 16, 17]. Strategies to increase the number of IPTp-SP doses and the coverage using reminders could improve this health intervention's effectiveness. This present project can be considered as a follow-up of the COSMIC study [18] recommendations whose objective was to determine the protective efficacy of community-scheduled screening and treatment (CSST) using community health workers (CHW) combined with other interventions against PM, the primary clinical outcome. Importantly, adherence to IPTp may be affected by perceptions, acceptability, and contextual factors that need to be understood and therefore improve the effectiveness of health interventions. In addition, the effectiveness of IPTp with sulfadoxine–pyrimethamine is threatened by parasite resistance. There is a progressively diminished efficacy of IPTp-SP in clearing existing infections and a shortening of the post-treatment prophylaxis period [19, 20]. Moreover, pregnant women can generally be infected with low parasites densities between ANCs compromising the outcome of the pregnancy [21]. These sub-infections will be missed in pregnant women due to the performance of current rapid diagnostic tests (RDTs), unable to detect low parasitemia. Nowadays, the new generation of ultrasensitive RDTs (US-RDTs) is being developed with the objective to detect lower density infections but data on their performance are scarce and conflicting in malaria-endemic areas [22–25]. Identifying sub-infections in pregnant women and clearing them with an effective artemisinin-based combination therapy (ACT) such as dihydroartemisinin–piperaquine (DHA-PQ) could improve the pregnancy outcome. DHA-PQ has been proven to be safe and effective, well-tolerated antimalarial with a long post-treatment prophylaxis effect based on the results of studies conducted in Nanoro and elsewhere [26–29]. There is a need to combine strategies in order to tackle the deleterious effects of malaria on both mothers and their offsprings. The main objective of the present study is to assess (1) the recruitment capability of the study sites and (2) feasibility of a study on integrated malaria in pregnancy prevention methods in rural Burkina Faso. The specific objectives are to assess perceptions, acceptability, and behaviors regarding the proposed methods by beneficiaries and service providers, (3) acceptability and behaviors regarding late attendance of ANCs of pregnant women, and (4) health care providers views on factors influencing pregnant women’s uptake of ANC interventions using an acceptability framework developed by Mandeep Sekhon et al.

## Methods

### Study design

This is a pilot individual randomized control trial in which all pregnant women attending the ANC will be invited to participate. They will be randomized into one of the intervention groups or the control group which is the standard of care. This feasibility study design will analyze the acceptability of the intervention through the dimension of the burden, ethical consequences, experience, opportunity cost, intention, and affective attitude and assess the impact and operational feasibility of adding malaria infection screening using an ultrasensitive RDT for placental and fetal outcomes. The analysis will focus on the factors limiting adherence to IPTp-SP uptake in the health district of Nanoro. We hypothesize that the intervention will improve pregnancy outcomes both in mothers and their offsprings by improving diagnosis, case management, and prevention of malaria in pregnancy.

### Study setting

The study will be carried out in the Nanoro health district, a rural area located in the center of Burkina Faso, at 85Km from Ouagadougou, the capital city. The health district of Nanoro covers an area of 150,000 inhabitants and comprises 18 dispensaries, all with maternity, general clinic, and immunization programs (EPI) [30]. The main local language is Mooré, though French is the official language and almost 80% of adults have a cell phone [31]. The Clinical Research Unit of Nanoro (CRUN) has set up the Nanoro Health and Demographic Surveillance System (HDSS) in this geographical area since February 2009. The HDSS currently covers 24 villages in Nanoro district, including over 60,000 inhabitants. Through the HDDS, every household as well as every inhabitant in the district has a unique identification number with GPS coordinates. The surveillance activities consist in visiting every household 3 times a year to collect data on vital events such as births and deaths, as well as migration, pregnancies, pregnancy outcomes, household assets, and access and use of key disease control interventions. HDSS provides also the core research framework for cohort studies and intervention trials [31]. Nanoro belongs to the Sudan-Sahel zone, with an estimated 58,868 recorded malaria cases in 2015 [30]. Oral quinine is used for the treatment of uncomplicated malaria in pregnancy in the first trimester while artemether-lumefantrine (AL) or DHA-PQ are recommended in the second and third trimesters of pregnancy [32].

### Recruitment

Prior to enrolment, community engagement activities will be implemented according to the CRUN procedures. Information provided will consist of a step-by-step approach, starting with the administrative leaders followed by the traditional chiefs and the community leaders and ending with the population in the study area. Community meetings and focus group discussions coordinated by the qualified research team member will be conducted in the villages of Soaw and Pella departments. The sessions will focus on the problem of malaria in pregnancy, the current strategies as well as their limitations. The need and the difficulties of improving the case detection will be discussed, as well as an outline of the proposed study, including the rationale, the background data available, and the study objectives. Finally, all pregnant women attending antennal care will be invited to participate in the present study.

### Eligibility criteria

All pregnant women attending the ANC will be asked to participate. The inclusion/exclusion criteria are as follows:

The main trial will include participants meeting the following eligibility criteria:

#### Inclusion criteria

Gestational age of 16 to 24 weeks at their first bookingAt least (≥) 16 years old (considered as an emancipated minor in Burkina Faso by the ethics committeeResidence in the study area and intention to stay in the area for the duration of the pregnancy and deliveryWilling to deliver at the health facilityWilling to provide biological samples as and when required during the study period (blood and placental biopsy)Ability to provide written informed consent

#### Exclusion criteria

A history of sensitivity to sulphonamides or to any of the study drugsHistory of known pregnancy complications or bad obstetric histories such as repeated stillbirths or eclampsiaHistory or presence of major illnesses likely to influence pregnancy outcome, including diabetes mellitus, severe renal or heart disease, or active tuberculosisAny significant illness at the time of screening that requires hospitalization, including severe malaria; Intent to move out of the study catchment area before delivery or deliver at relative’s home out of the catchment areaPrior enrolment in the study or concurrent enrolment in another study

### Randomization and blinding

Eligible pregnant women will be randomly assigned (1:1) to either an intervention or control group computer-generated randomization schedule. Allocation concealment will be achieved by the use of sealed, opaque, and sequentially numbered envelopes each containing the study number and assignment of the participant to the study group. These envelopes will be prepared by an independent pharmacist based on the block randomization list generated by the study statistician. Once the participant has met all the eligibility criteria, the study clinician/nurse will open the envelopes to determine the group assignment and the study number of the participant. Recruitment will be “competitive” between the sites in the trial. Participants will be recruited over a 12-month period and followed for 6 months until delivery. To minimize cross-contamination, study subjects will be encouraged to attend the health facility within their catchment and not seek ANC or delivery elsewhere. It will not be possible to blind this intervention as pregnant women will quickly identify into which group they have been randomized into. Observer bias will be reduced where feasible. Blood films and placenta biopsies will be read by microscopists blinded to the identity and intervention status of the subjects.

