### Statistical methods

The randomization will ensure a balanced distribution of baseline characteristics between the two groups. A descriptive methodology will be used to analyze feasibility outcomes. Variables such as completion of the study participants recruitment within 12 months, the percentage of refusals, perception, and acceptability will be summarized per group. The primary clinical outcome will compare the prevalence of placental malaria (defined as the number of positive samples by the total number of samples) in each group and will be examined with logistic regression. This will be adjusted by gravidity, parity, season, and number of DHA-PQ. Appropriate statistical methods will be used to account for the influence of potential confounders (number of SP doses, number of co-morbidities, co-medication, the season of malaria transmission, gravidity, etc).

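### Several sites recruit in parallel from a blocked envelope list, but study site is not among the covariates named for the primary logistic model

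*Protocol article*

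**What the plan says.** All references are to the protocol article.

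- **Randomization and blinding:** women are allocated individually in a 1:1 ratio from a list produced by computer. The concealment device is stated as follows: "Allocation concealment will be achieved by the use of sealed, opaque, and sequentially numbered envelopes". On who prepares them: "These envelopes will be prepared by an independent pharmacist based on the block randomization list generated by the study statistician". On who opens them, and when: "Once the participant has met all the eligibility criteria, the study clinician/nurse will open the envelopes to determine the group assignment". Recruitment is described as competitive between sites. The trial is open, but "Blood films and placenta biopsies will be read by microscopists blinded to the identity and intervention status of the subjects".
- **Primary feasibility outcomes:** the coordinator follows weekly enrolment at each study site from the screening and recruitment log, so site is recorded for every woman.
- **Statistical methods:** the primary clinical outcome is compared by logistic regression, and "This will be adjusted by gravidity, parity, season, and number of DHA-PQ". A further, open-ended list of possible confounders follows, and a later paragraph names adjustment factors for other models as examples. Site appears in none of these.
- **Sample size considerations:** placental malaria falling from 40% to 25%, 80% power, 5% significance, 152 women per group, raised to 170 for 10% loss.

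**The concern.** Where several facilities enrol at once from numbered envelopes, the natural arrangement is for each to hold its own run of envelopes, and blocks then tend to balance the arms within each site. If placental malaria also differs between sites, an analysis that ignores site counts between-site variation as noise, although the allocation has already removed it from the comparison of arms. The standard error is then slightly too large, the test is conservative and some power is given away. The explicit covariate sentence is where a reader would expect site to be named.

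A second question comes from the same section. In an open trial with a blocked list, staff who see past assignments may be able to anticipate some later ones.

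**Working it through.** **1. The plan's own figure.** Two-sided 5%, 80% power, 40% against 25%, pooled variance, no continuity correction gives 152 per group, as stated. 152/0.9 = 168.9, so 169, against the stated 170. The sample size is sound and this point does not change it.

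**2. Assumptions for the site check.** The article gives neither the number of sites nor prevalence by site. I assume two equal sites, 76 evaluable women per arm at each (152 per arm), arms balanced within site, mean control prevalence 40%, mean intervention prevalence 25% and a common odds ratio across sites. The other named covariates are left out.

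**3. Type I error without site.** The test that ignores site uses variance 0.40 × 0.60 = 0.24. The variance that applies is the mean within-site variance.
- 30%/50%: (0.21 + 0.25)/2 = 0.23; ratio 0.23/0.24 = 0.958; effective critical value 1.96/√0.958 = 2.002; actual level 4.5%.
- 25%/55%: (0.1875 + 0.2475)/2 = 0.2175; ratio 0.906; 1.96/√0.906 = 2.059; actual level 4.0%.

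With site in the model the level is 5% by construction in this approximation.

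**4. Power.** Power = Φ((0.15 − c)/SE). SE is the true standard error given balance within site, and c is 1.96 times the null standard error that the test uses. Without site, c = 1.96 × √(2 × 0.325 × 0.675/152) = 0.1053 throughout. With site, c uses the mean over sites of p̄(1 − p̄), where p̄ is the average of the two arms at that site.

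| Control prevalence (assumed) | Intervention prevalence | SE | c with site | Power without site | Power with site |
|---|---|---|---|---|---|
| 40%/40% | 25.0%/25.0% | 0.0530 | 0.1053 | 80.0% | 80.0% |
| 30%/50% | 17.3%/32.7% | 0.0520 | 0.1034 | 80.5% | 81.5% |
| 25%/55% | 13.5%/36.5% | 0.0508 | 0.1010 | 81.1% | 83.3% |

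The gain is 0, 1.0 and 2.2 percentage points. A simulation with 200,000 trials per scenario agrees. At 25%/55% the unadjusted test rejects 4.2% of the time under the null and the site-adjusted logistic model 5.0%; power is 81.4% and 83.5%.

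**5. A wider range.** A separate simulation assumed four sites of 76 women, with site effects of standard deviation 0, 0.3, 0.6 and 1.0 on the log-odds scale. Power without and with site was 80% and 80%, 79% and 80%, 76% and 77%, 70% and 75%. Type I error without site was 3.75% to 4.85%, so it was never inflated. The 5-point loss needs very large differences between sites.

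**6. Predictability (secondary).** For a fixed 1:1 block of length 2m whose length is known and which is used in order in front of one observer, the share of assignments known with certainty is 1/(m + 1). That is 33% for an assumed block of 4, 25% for 6, 20% for 8 and 17% for 10. These are upper figures, and they fall if block lengths vary or are withheld.

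**The case against.** The best defence is that the adjustment set is not closed. The confounder list in Statistical methods is open-ended, and the final set may be settled in an analysis plan that is not shown. The article also does not say that the list is stratified or split by site. Without balance within site, the test that ignores site is not conservative, so that part of the argument is conditional. The power gain is small in any case. All of this stands, and it limits the point to an inexpensive improvement. What remains is that the one sentence fixing the primary model names four covariates and leaves out a recorded feature of how recruitment is organised.

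A reader might go further and infer that the nurse can work out coming assignments and that the primary comparison is therefore biased. The article does not support this. It does not say that blocks are fixed or that their length is known to staff, that envelopes are kept at the recruiting sites, or that the person opening them also judges eligibility. It does state safeguards: opaque envelopes, independent preparation, opening only after eligibility is met, and blinded reading of the placental biopsies. Block length is a detail that an article may leave to the full protocol. If half of primigravidae were deferred whenever control was guessed (assumed risks 55% against 34%), the crude bias would be only about 1 percentage point, against a planned effect of 15. That selection acts through gravidity, which the primary model already includes.

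**Conclusion.** The point holds as a modest matter of efficiency and calibration. Study site belongs in the primary model and is not named there. Under assumed two-site control prevalences from 30%/50% to 25%/55%, with balance within site, including it adds about 1 to 2 points of power and returns a slightly conservative test (about 4.0% to 4.5%) to its nominal level. With little variation between sites nothing is gained or lost. Leaving site out does not inflate type I error, and putting it in would not repair selective enrolment if that occurred.

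Predictable allocation is a conditional risk only. Its size of 17% to 33% rests on assumed fixed, known blocks of 10 down to 4, and the article neither confirms nor excludes them.

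**What to change.** In Statistical methods, add study site to the named covariates of the primary logistic model as a fixed baseline effect, with very small sites pooled by a rule set before the data are analysed. Do the same in the secondary models. The cost is one variable already held in the recruitment log and a few degrees of freedom. It can be done whatever the stage of recruitment, preferably before outcomes are compared by group.

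Separately, check the full protocol for varying block lengths withheld from the staff who open envelopes, and for whether the list is generated by site. If both are there, no action is needed. Recruitment began in August 2020 for one year (Trial status), so any change to the envelopes may be relevant only to the main trial that this pilot prepares.

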### Intervention description

In this study, 2 packages will be used as comparators: the standard of care package versus the new intervention package.

The current standard of care strategy for pregnant women attending ANC during the second and third trimester of pregnancy is based on three components (standard RDTs, AL, and scheduled visits without reminder).

The new intervention package will include three components (US-RDTs, DHA-PQ, and phone call reminders). Each of these three components has been shown to individually improve pregnancy outcomes. We hypothesize that a synergistic action of the three components will result in a higher impact on the outcomes of interest (placental malaria infection, low birth weight, and peripheral malaria infection at delivery) as compared to the current standard of care.

Comparisons will not be done between the individual components of each intervention package, but rather their combined effects between study groups: the intervention group (ultrasensitive malaria RDTs, DHA-PQ, and phone reminder) and the control group (the standard of care described above which includes standard RDT, AL, and scheduled visit without reminder).

